To examine the effectiveness of brief mindfulness intervention in reducing smoking cravings, this study employs a randomized controlled parallel trial design. Expanding upon existing literature that supports the positive effects of brief mindfulness interventions, the primary aim of this study is to establish the superiority of brief mindfulness intervention over the control group within the intervention conditions. The trial consists of four distinct stages: participant recruitment, baseline measurement, measurement during the intervention period, and follow-up measurement. After the completion of each stage, pertinent evaluations will be conducted to assess the outcomes. The design flowchart, depicted in **Fig 3.**, illustrates the methodology employed in this study. It is important to note that the trial has not yet begun, and it is expected that the entire process, including participant recruitment, data analysis, and article writing, will take approximately one year. Additionally, a follow-up period of one year will be conducted to assess the long-term effects of the intervention.

**
[figure not shown]
**

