**Fig 3. Study Design and Procedure**

*The upper portion of the figure illustrates the overall study design. The middle portion depicts the timeline for assessing scales and EEG at baseline, post-intervention, and follow-up timepoints. Brief mindfulness and relaxation training will be administered to both the intervention and control groups after recruitment. The baseline assessment (-T1, T0) will be completed before the intervention. Audio guidance will be provided for daily practice in the BMT group, while there will be no additional practice or intervention for the control group after training. The lower portion of the figure represents the modules of psychological and behavioural assessments during the baseline and five follow-up sessions. The cue-reactivity task will be implemented using a customized two-choice oddball paradigm. INT: intervention, rs-EEG: resting-state EEG; BMT: brief mindfulness training; VAS: Visual analogue scale; SMT: state-mindfulness.*

1. ***Sample size estimation. [List the four elements: δ(Δ) or π1, π2, α, β or Power, and provide the calculation formula]***

In this study, the subjective reports of smoking urges (QSU-Brief) will be used as the primary outcome measure. Referring to study of similar populations **^[28]^**, We set δ(Δ)_tot_ = 4 to represent the anticipated reduction of 4 points in the QSU-Brief score after the intervention in the experimental group. Multiple measurements of the QSU-Brief will be conducted on participants before and after the training, as well as during the 60-minute online training period. To estimate Cohens’d, we have set α = 0.05 and β = 0.80. Cohens’d can be calculated using the formula Cohens’d=(δ(Δ)/SD_estimate_), where the estimated SD_estimate_ was 7.65 based on reference study. Therefore, the corresponding command is pwr.t.test (d=cohens_d, sig.level = 0.05, power = 0.80, type = "paired", alternative = "two.sided"), and the estimated sample size is 34. Therefore, the minimum required sample size for the experimental group is 34. Considering a natural dropout rate of 30%, the sample size for the experimental group should be no less than 45.

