1. ***Methods of randomization and concealed allocation. [Randomization is used to reduce the risk of selection bias. Methods for generating random number sequences include computer software, random number tables, semi-random or pseudo-random methods (such as using dates, birthdays, or even/odd numbers of hospital visits). Please describe the individuals involved in generating random number sequences and the methods they use. Concealed allocation is used in treatment studies to reduce the risk of selection bias. Key steps in concealed allocation include having a designated person determine the allocation sequence, ensuring that this person is not involved in enrolling participants, and securely storing the allocation table. Please provide detailed descriptions of these steps. Central randomization is a robust method of concealed allocation. Describe the individuals and methods involved in determining the allocation sequence]***

(1) In this study, the intervention period for the BMT, which is a behavioural training, lasts for one week. Baseline data, including EEG data, will be collected from all participants. Following this, there will be a one-week training period for the intervention content, after which post-intervention data, including scales, self-reports, and EEG data, will be collected. Follow-up measurements will be conducted at 1 week, 1 month, 3 months, 6 months, and 1 year after the trial's completion. Group allocation will be performed after the completion of baseline data collection.

(2) The primary intervention method employed in this study is the brief mindfulness-based intervention of "STOP" **^[29, 30]^**, with a 7-day ~60-min sessions mindfulness course for the experimental group. Meanwhile, the control group will undergo relaxation training. All recruited participants are from the same school, and due to the lack of blinding execution conditions, achieving double-blind standards may present challenges.

(3) The randomization process for this trial will involve the use of a random sequence generator website (https://www.random.org/). This website will be utilized to ensure the random assignment of participants to either the experimental or control group.

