| **Anxiety** | -T1 | **Generalized Anxiety Disorder (GAD-7)** used to measure anxiety related problems over the past two weeks, with each project scoring 0-3 points and a total score of 0-21 points **^[25]^**, with scores of 5, 10, and 15 corresponding to the cutoff values for "mild", "moderate", and "severe" anxiety levels **^[45]^**. | others |

*CR: cue-reactivity.

1. ***Definition of Participant Effectiveness Determination. [This includes definitions for participant withdrawal, exclusion, loss to follow-up, confounding factors, study discontinuation, and study suspension]***

(1) **Participant Withdrawal:** Each participant has the right to withdraw from the study at any time without the need to provide a reason. Participants who choose to withdraw voluntarily will not be included in the analysis. As part of our comprehensive research procedure, we have established a protocol for managing participants who decide to withdraw. If participants are willing to provide a reason for their withdrawal, it will be documented and recorded.

(2) **Participant Exclusion:** Due to the inability to ensure full intervention participation in the intervention group during the training process, the "STOP" training period lasts for one week. Participants who have participated in less than 5 training sessions will be considered as not having received the complete intervention and, theoretically, should be excluded or adjusted using mixed effects models.

(3) **Participant Loss to Follow-up:** If a participant cannot be contacted for two consecutive visits after the completion of the intervention for any reason, they will be classified as lost to follow-up.

(4) **Participant Contamination:** Following the completion of the intervention, a survey will be conducted with the participants. If the control group attempts to learn about the training mode used by the intervention group (or vice versa) and attempts to replicate the training, they will be classified as contaminated participants.

(5) **Participant Termination:** To prioritize participant health, any adverse events (including tobacco withdrawal symptoms) will be considered termination criteria. Researchers will discuss with the participant who experiencing such conditions and terminate the intervention early. Participants will receive appropriate clinical interventions only with their explicit consent.

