All data will be analyzed upon completion of data collection. The data analysis process will strictly adhere to the principles of the blind method. Analysis of the data will be conducted using R software (https://www.r-project.org/), IBM SPSS Statistics for Windows, V20.0 (SPSS), MATLAB (MathWorks in Natick, Massachusetts, USA), and EEGlab (https://sccn.ucsd.edu/eeglab). Descriptive statistics will be used for demographic, psychological, and behavioural data at baseline. Two-sample t-tests and χ^2^ tests will be performed for continuous and categorical variables between the intervention group and control group. Repeated measures MANOVA will be adopted to examine intervention effects while adjusting for individual factors and pre-intervention variables (e.g., trait mindfulness and smoking indices). Within-group effects will be investigated through serial trend analysis from -T1 to T5. Linear mixed-effects model analysis will include data from all measures at different timepoints to explore factors associated with smoking cue-reactivity for both groups. EEG data will be preprocessed using Matlab software and the EEGLab toolbox. Relative spectrum power for six EEG bands (delta: 1-4Hz, theta: 4-8Hz, alpha: 8-13Hz, low-beta: 13-20Hz, high-beta: 20-30Hz, and low-gamma: 30-48Hz) will be calculated at the single electrode and ROI level. Microstate and phase synchronization analysis will be conducted, and source localization analysis will be used to investigate functional changes in subcortical brain regions. Repeated measures analysis of variance and simple effect analysis will be performed for EEG indices, considering significance in the professional field. Effect size will be measured using Cohen's d or partial eta-squared values **^[46]^**.

1. ***Participant management system.***

(1) **Contact and Guidance:** A contact group consisting of relevant researchers is responsible for providing guidance and addressing any study-related questions for participants throughout the entire study period. This ensures that participants have a clear understanding of the study and can actively cooperate with the research process. Researchers are required to respond promptly and keep records for participants who withdraw, are excluded, lost to follow-up, terminated, or suspended.

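### Voluntary withdrawers are excluded from the analysis whenever they leave, so randomised participants and their observed outcomes are removed after allocation

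*Protocol*

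**What the plan says.** All references are to the protocol.

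- **Definition of Participant Effectiveness Determination, item (1):** "Each participant has the right to withdraw from the study at any time without the need to provide a reason". Then: "Participants who choose to withdraw voluntarily will not be included in the analysis". On reasons: "If participants are willing to provide a reason for their withdrawal, it will be documented and recorded".
- **Same section, item (3):** a participant who "cannot be contacted for two consecutive visits after the completion of the intervention" counts as lost to follow-up. Nothing is said about removing that person from the analysis.
- **Same section, items (2), (5) and (6):** fewer than five training sessions, termination for an adverse event, and suspension are separate categories. Only item (6) states in words that data gathered earlier are dropped.
- **Methods of randomization and concealed allocation:** "Group allocation will be performed after the completion of baseline data collection".
- **Study design:** "the primary aim of this study is to establish the superiority of brief mindfulness intervention over the control group".
- **Sample size estimation:** "Considering a natural dropout rate of 30" percent, the experimental group is set at no fewer than 45.
- **Statistical analysis methods:** "Linear mixed-effects model analysis will include data from all measures at different timepoints". The template heading asks about intention-to-treat and per-protocol analyses, but the text beneath it names neither.

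**The concern.** The subject of the exclusion sentence is the participant, not the data that would have come after withdrawal. Read plainly, someone who attends every session, completes T1 and withdraws at the 6-month visit is left out of the T1 comparison as well.

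The groups that remain are then partly self-selected. Differential withdrawal is plausible here: the Blinding section says double-blinding is not feasible, and the Fig 3 legend gives the BMT arm daily audio-guided practice while the control arm has none after training.

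Inclusion also depends on how a person leaves. Someone who declares withdrawal is excluded. Someone who falls silent is lost to follow-up, with no deletion rule stated.

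A mixed model does not repair this, because it cannot use participants whom the rule has already removed.

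**Working it through.** **Reading the rule against the rest of the protocol**

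1. Allocation comes after baseline, so a withdrawal during training or follow-up is post-randomisation. A withdrawal before allocation does no damage to the randomised groups.
2. The stated aim is a between-group comparison, which relies on intact randomised groups.
3. Nothing under Statistical analysis methods restores withdrawn participants. The mixed-model sentence concerns measures and timepoints, not who is in the analysis set.

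**Inputs for scale**

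From Sample size estimation: planned change 4 points, SD 7.65, dropout 30%, experimental group 45 (34 × 1.3 = 44.2, rounded up). Assumed, because the protocol does not give them: 45 controls, arm-specific withdrawal rates, the strength of selection, and that all dropout is voluntary withdrawal. The SD appears in a paired calculation and is used here as a between-person SD.

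**Bias, simple model**

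Assume no true effect. Let p be the share withdrawing and g the number of points by which withdrawers are worse than completers. If an arm's overall mean is 0, its completer mean is −p·g, so the bias is −(p_BMT·g_BMT − p_ctrl·g_ctrl). Size of the bias in favour of BMT, in points:

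| Scenario | g = 2 | g = 4 | g = 7.65 |
|---|---|---|---|
| 30% in each arm, same g | 0 | 0 | 0 |
| 30% BMT, 15% control, same g | 0.3 | 0.6 | 1.15 |
| 30% BMT, selection in BMT only | 0.6 | 1.2 | 2.3 |

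The last row is 15%, 30% and 57% of the planned 4 points.

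**Bias, normal selection model**

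The shift in an arm is r × 7.65 × φ(z_p)/(1 − p), where r is the correlation between withdrawal and craving.

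- *Scenario A:* 30% v 15%, r = 0.5. Shifts 1.90 and 1.05; bias 0.85; SE 1.84; type I error 7.5%.
- *Scenario B:* 20% in each arm for opposite reasons, r = 0.3. Shift 0.80 in each arm; bias 1.61 before rounding the shifts; SE 1.80; type I error 14.5%.

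**How much of this the fix removes**

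Suppose half of the withdrawers, taken at random, leave after T1 and their T1 values are kept. With simple means, each arm's shift becomes shift × (1 − p)/2 ÷ (1 − p/2).

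- *A:* 1.90 × 0.70/2 ÷ 0.85 = 0.78, and 1.05 × 0.85/2 ÷ 0.925 = 0.48. The bias left is 0.30 (type I error 5.4%).
- *B:* 0.80 × 0.80/2 ÷ 0.90 = 0.36 in each arm. The bias left is 0.71 (type I error 7.0%).

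So 0.30/0.85 = 35% and 0.71/1.61 = 44% of the bias remains.

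**Precision at T1**

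After a 30% loss, 45 × 0.70 = 31.5, about 31 per arm. If half of that loss comes after T1 and is kept, 45 × 0.85 = 38.25, about 38 per arm. The SE ratio is √(31/38) = 0.903, a cut of about 10%. This step needs no assumption about selection.

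**The case against.** Several stronger readings are tempting, and the protocol does not support them.

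- **Harms behind a withdrawal disappear.** Not supported. An adverse event is a termination criterion under item (5), separate from voluntary withdrawal. Symptoms are asked about daily during the intervention, and the Participant management system section requires records for those who withdraw. What stands is narrower: no text says that withdrawers' recorded events enter the analysed results, and reasons for withdrawal are noted only if offered.
- **The protocol orders deletion of data already collected.** That is the plain effect of excluding the participant, but those words are printed only for suspension in item (6).
- **Thirty percent will withdraw.** The 30% is general dropout, not divided among withdrawal, loss, termination and suspension.
- **The bias figures are the cost of this rule.** They measure all informative dropout. Someone who leaves before T1 has no T1 value to keep. If everyone left before T1, the fix would remove almost none of the bias, apart from what a mixed model recovers from baseline. Scenario B also needs opposite selection in the two arms, for which the protocol gives no evidence.
- **The protocol confuses stopping training with leaving the study.** Incomplete training, termination and suspension have their own items. Consent to data use normally sits in the consent form, which is not in this copy, so silence on it is not a defect.

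It can also be said that analysis sets belong in a statistical analysis plan. Leaving them to that plan would be acceptable. Here the protocol fixes a rule, and a later plan could undo it only by contradicting it.

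**Conclusion.** The point holds as a defect in the analysis set. As written, the rule removes randomised participants after allocation, discards outcomes already observed, and treats declared withdrawal differently from silent loss.

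The direction and size of the bias cannot be derived from the protocol. The 0 to 2.3 point range rests on assumed rates, assumed selection and, in the normal selection model, an unstated control-arm size. In the two scenarios worked through, the fix takes 0.85 down to about 0.30 and 1.61 down to about 0.71, if half of the withdrawers leave after T1. The precision gain of about 10% in the SE rests on that same timing, a 30% loss and 45 per arm.

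On harms, the conclusion is only that withdrawers' events could be missing from the reported results. They are not missing from the records. The rule bears on the primary comparison and should be changed before the trial starts; the Study design section says that recruitment has not begun.

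**What to change.** Replace the exclusion sentence in item (1) with wording such as:

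> All randomised participants are analysed in their allocated arm. Data collected up to withdrawal are used in a mixed model, unless the participant revokes consent to their use. Adverse events recorded before withdrawal are included in the safety summary. Withdrawals, and any reasons given, are reported by arm. A completer analysis is a sensitivity analysis only.

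Reconcile item (2), on fewer than five sessions, and item (6), on suspension, with this analysis set. Otherwise they would conflict with the new sentence.

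The cost is a small amount of protocol wording and analysis work, with no added participants. Inviting those who stop training to the visits already scheduled is optional. It would reduce the missing data further, but it takes effort, since T1 to T5 each include a 64-channel EEG recording.

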  8. Insert the active electrodes with labeled channels into the corresponding electrode names on the EEG cap (be careful to match the labels of the active electrodes with the EEG cap). Wrap the CMS and DRL active electrode wires around the cables of the other electrodes (wrap them 3-5 times), and plug their connectors into the corresponding ports of the amplifier.
  9. After confirming that the EEG software and hardware are properly connected, run the software for collecting EEG data. Follow the instructions of the software and confirm that the quality of the EEG data meets the standards before starting the data collection. Save the EEG data to the computer or hard drive according to the naming format.

(2) **Procedure for brief mindfulness training:** The researchers of this experiment will collaborate with professional psychology teachers for a one-week training on intervention content. Prior to each practice session, participants will be reminded of the training's schedule and location, and researchers will be present to sign in on site. The one-week training on intervention content will be conducted by professional teachers from the Students Counseling and Mental Health Center at Kunming University of Science and Technology. The training will be led by experienced psychology teachers, and the content for each day's practice will be shared with participants through their group chat for continued practice after each session.

1. ***Statistical analysis methods. [Select appropriate statistical analysis methods based on the data type of each measurement variable. Include any additional methods for subgroup analysis or auxiliary analysis. If there are personnel reductions during the trial, indicate whether an intention-to-treat (ITT) analysis was used and compare it with per-protocol (PP) analysis]***

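### The under-5-sessions rule excludes or adjusts on attendance after randomisation, most naturally in the mindfulness arm only, so it does not preserve the randomised comparison behind the superiority aim

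*Protocol*

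**What the plan says.** The Study design section describes a randomised parallel trial in which "the primary aim of this study is to establish the superiority of brief mindfulness intervention over the control group".

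Under Definition of Participant Effectiveness Determination, item (2) Participant Exclusion opens with the "inability to ensure full intervention participation in the intervention group" and refers to the one-week STOP training. It then says: "Participants who have participated in less than 5 training sessions will be considered as not having received the complete intervention". Its consequence is that they "theoretically, should be excluded or adjusted using mixed effects models".

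The randomization section identifies STOP as the experimental intervention, a 7-day course. It gives the control group relaxation training without a number of sessions. In the Standard operating procedures, the only training procedure is the one for mindfulness, where "researchers will be present to sign in on site".

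Two neighbouring items also remove people or data: item (1) leaves voluntary withdrawals out of the analysis, and item (6) drops data collected before a suspension.

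**The concern.** Allocation follows baseline, so the number of sessions attended is a post-randomisation behaviour, plausibly related to motivation, craving and tolerance of the training. The protocol itself supplies one link. Item (5) makes adverse events, including tobacco withdrawal symptoms, a reason to end the intervention early, and the adverse events section counts craving among those symptoms. A BMT participant stopped before the fifth session would fall under item (2). A relaxation participant in the same position has no stated threshold to fall under.

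If low attenders leave one arm only, the arms being compared are no longer those that randomisation made alike. BMT could look better because its less motivated members were removed. It could look worse if those removed were smokers who were cutting down. Either way, the difference would not be the effect of being assigned to BMT.

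**Working it through.** **Does the rule keep the comparison as randomised?** There are three readings.

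1. *Exclusion, BMT only.* This is the natural reading, because the lead sentence names the intervention group and STOP, and relaxation has no session count to which a threshold of 5 could apply. BMT participants with at least 5 sessions would be compared with relaxation participants not selected on attendance.
2. *Exclusion, both arms.* This is a per-protocol comparison of attenders. It is not a comparison of the groups as randomised.
3. *Adjustment with mixed models.* The item names no model terms. If all randomised participants stay in and no attendance term is fitted, the comparison is preserved. If sessions attended enter as a covariate, the model conditions on a post-randomisation variable with no defined counterpart in controls. The Statistical analysis section does not settle this: it assigns intervention effects to repeated measures MANOVA and gives the mixed model an exploratory purpose.

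**How large could reading 1 be?** The rule carries no figure of its own to reproduce, so this is an illustration.

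Inputs from Sample size estimation: SD 7.65, a planned QSU-Brief reduction of 4 points, 45 in the experimental group, two-sided 5% level. (The 45 serves only as a group size here. How it was derived is a separate matter.)

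Assumptions not in the protocol: 45 controls; no true effect; a share p of BMT below 5 sessions of 10%, 20% or 30%; a correlation r between attendance propensity and lower craving of 0 to 0.5; no baseline adjustment.

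Formulas, with φ the standard normal density and z_p the p-quantile:

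- bias = r × 7.65 × φ(z_p) / (1 − p)
- SE = 7.65 × √(1/(45(1 − p)) + 1/45)
- type I error = P(|Z + bias/SE| > 1.96)

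For p = 0.2, r = 0.3: φ(z_p) = 0.280; bias = 0.3 × 7.65 × 0.280/0.8 = 0.80; SE = 7.65 × √(1/36 + 1/45) = 1.71; bias/SE = 0.47; type I error 7.6%.

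For p = 0.3, r = 0.5: φ(z_p) = 0.348; bias = 0.5 × 7.65 × 0.348/0.7 = 1.90; SE = 7.65 × √(1/31.5 + 1/45) = 1.78; bias/SE = 1.07; type I error 18.8%.

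A simulation under the same assumptions (20,000 replicates, t test, whole participants removed from BMT only) gave the type I errors below. The biases are from the formula.

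| Removed from BMT | r = 0 | r = 0.1 | r = 0.3 | r = 0.5 |
| --- | --- | --- | --- | --- |
| 10% | 0; 5.0% | 0.15; 5.3% | 0.45; 6.0% | 0.75; 7.9% |
| 20% | 0; 5.1% | 0.27; 5.2% | 0.80; 7.6% | 1.34; 12.6% |
| 30% | 0; 5.2% | 0.38; 5.6% | 1.14; 9.8% | 1.90; 19.8% |

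(Cells: bias in QSU-Brief points; two-sided type I error.)

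The largest bias is 1.90/4 = 47% of the planned 4 points. When the same rule was applied to both arms, with equal shares and correlations, type I error stayed at about 5% to 6%. The one-sided removal therefore drives the error in this model.

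**The case against.** The best reply is that the item is hedged and says less than a critic might infer. Four stronger readings are tempting, and the documents support none of them fully.

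- *That the rule is written for BMT only.* The operative sentence says participants, without naming an arm. The restriction comes from the sentence before it and from the lack of any relaxation threshold. The sign-in evidence is weak, because no relaxation procedure is described at all. If the rule covers both arms, the figures above do not apply, but exclusion still gives a per-protocol comparison.
- *That the plan adjusts for attendance.* It says only that such participants are "should be excluded or adjusted using mixed effects models" and names no covariate. The fair criticism is that this branch is undefined.
- *That BMT attenders would face every relaxation participant.* Items (1) and (6) remove withdrawals and pre-suspension data without limiting this to one arm.
- *That open-label staff will choose between the two options after seeing results.* Blinding researchers is called challenging and the choice is left open, but the Statistical analysis section commits to blinded analysis. Such a choice is possible; it is not planned.

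Two further objections stand. The size rests on assumed shares, correlations and control numbers, and on an SD taken from a paired, within-group calculation; the planned adjustment for pre-intervention variables would absorb part of any link that runs through baseline. Also, a protocol may leave the naming of analysis sets to a statistical analysis plan, so that silence is not the fault here. The fault is a rule the protocol does state, which an as-randomised analysis named elsewhere would contradict.

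**Conclusion.** The concern holds in this form: item (2) allows an exclusion on post-randomisation attendance that most naturally falls on BMT alone, and its alternative is too vague to count as a safeguard. Nothing else in the protocol restores an as-randomised comparison for the superiority aim. This conclusion is structural and needs no assumed numbers.

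The size is only illustrative. Under the assumptions listed, the bias runs from 0 to 1.9 QSU-Brief points and two-sided type I error from 5% to about 19-20%. With no correlation between attendance and outcome there is no bias. The direction is uncertain, since the correlation could have either sign.

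**What to change.** Replace item (2) with wording such as: *All randomised participants are analysed in the arm assigned, whatever number of sessions they attended, using all available data. This is the primary analysis, and its model contains no term for sessions attended.*

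Then:

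- reconcile items (1) and (6) with that statement, keeping data already collected unless the participant withdraws consent for its use; otherwise the three items would conflict;
- record attendance in the same way in both arms;
- use the 5-session threshold only in a labelled secondary per-protocol analysis, with a matching definition for relaxation, which requires the protocol to state how many relaxation sessions there are.

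The cost is protocol wording, an attendance sheet for the relaxation sessions and a possibly smaller estimated BMT effect. The Study design section says the trial has not begun, so the change can be made before anyone is affected.
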